### 3.2.3 *Time-dependent analyses*

Time-dependent analyses will be used to assess the impact of “exposure to the program” on the rate of hospitalisations. Exposure to the program will be defined for each semester as the proportion of the time a participant was exposed to the program e.g. if a patient gets enrolled into the program halfway through a semester, his/her exposure will be 50% (s/he was on the program 50% of the time during that particular semester).

The time-dependent analysis will cover a total of 6 semesters. All patients enrolled between January 2011 and December 2013 will be included and all events occurring within the same timeframe will be considered. For the purpose of this analysis every program participant will therefore contribute 6 data points; one per semester. The analysis will be a Poisson regression with the exposure proportion as a fixed effect. A sensitivity analysis will also include the semester and its interaction with exposure. Generalized estimating equations with a compound symmetry structure will be used to model the correlations between multiple measurements from each patient

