### 3.2.4 *Adjusted analyses*

Both the before-after and the time-dependent analyses will be performed without and with adjustment. Potential covariates will include LHD, age, gender, aboriginality, ARIA, SEIFA, target conditions, SF1 and previous patterns of service utilisation (number of hospitalisations in 2010, number of unplanned hospitalisations in 2010, number of avoidable hospitalisations in 2010 and number of ED admissions in 2010).

Each potential covariate will first be analysed using a univariate Poisson regression and only those with a univariate p-value smaller than 0.20 will be included in the final model. To avoid problems due to colinearity, in case of two covariates with a Pearson correlation coefficient greater than 0.8, only the one with the smallest univariate p-value will be kept in the final model. For covariates with more than 10% of data missing, we will create a separate category labeled “missing”.

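### The main time-dependent model has no semester term, so a common calendar trend in admission rates is absorbed into the exposure effect of this supporting analysis

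*SAP*

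**What the plan says.** Section 3.2.3 of the SAP defines the exposure variable: "Exposure to the program will be defined for each semester as the proportion of the time a participant was exposed to the program". The window is fixed: "The time-dependent analysis will cover a total of 6 semesters". So is the population: "All patients enrolled between January 2011 and December 2013 will be included". Each person supplies a full set of rows: "every program participant will therefore contribute 6 data points; one per semester". The main model is then stated: "The analysis will be a Poisson regression with the exposure proportion as a fixed effect". Within-person correlation is handled by GEE with a compound symmetry structure.

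Semester appears once: "A sensitivity analysis will also include the semester and its interaction with exposure". The SAP does not say whether semester is coded as a factor or as a linear term.

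Section 3.2.4 repeats the analysis with adjustment: "Potential covariates will include LHD, age, gender, aboriginality, ARIA, SEIFA, target conditions, SF1 and previous patterns of service utilisation", the last of these being counts from 2010. None of them is calendar time. Section 3.3.1 names the propensity-matched comparison as the primary analysis of program effect.

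**The concern.** Everyone in this model is a participant who enrols at some point in the six semesters, and there are no never-exposed controls. The SAP describes entry into the program but no exit. On that definition each person's exposure runs from 0, through a fraction in the enrolment semester, to 1, and does not fall. Early semesters are therefore mostly unexposed and late semesters mostly exposed. If admission rates drift over 2011-2013 for reasons unrelated to the program, such as a change in coding or admission practice, a model containing exposure alone has nowhere else to put the drift.

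The adjusted version does not help. Its covariates are baseline characteristics and 2010 counts; used as such they are constant across a person's six rows and cannot absorb a change over time.

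The sensitivity analysis does not settle it either. Because semester comes in together with its interaction with exposure, the result is an exposure effect that varies by semester. If it differs from the main result, the reader cannot tell confounding by time from an effect that changes over time. The one model that separates them, exposure plus semester without the interaction, is not planned. Enrolment is staggered, so the data would support it.

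**Working it through.** The SAP gives no effect size, trend or sample size for this analysis, so there is no stated figure to reproduce. The check asks what the planned model estimates when the true program rate ratio is 1.00.

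**Inputs from the SAP.** Six semesters; participants only; exposure equal to the share of the semester on the program, with no exit; Poisson GEE with compound symmetry.

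**Assumptions, not in the SAP.** A log-linear calendar trend of t per semester; uniform, front-loaded or back-loaded enrolment; 0.3 events per semester at the start; working correlation 0.05, 0.15 or 0.40.

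**Step 1: how closely exposure follows calendar time.** Under uniform enrolment, mean exposure in semester k is (k - 0.5)/6: 0.08, 0.25, 0.42, 0.58, 0.75, 0.92.
- Variance of k over 1 to 6 is 35/12 = 2.917.
- Covariance of k and exposure is 2.917/6 = 0.486.
- The mean of squared exposure in semester k is (k - 1)/6 + 1/18, averaging 0.4722 over semesters. The variance of exposure is 0.4722 - 0.5² = 0.2222.
- Correlation = 0.486/√(2.917 × 0.2222) = 0.60.

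Front- and back-loaded enrolment give about 0.65.

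**Step 2: approximate size by hand.** If the log rate changes by ln(1 + t) per semester and semester is left out, the exposure coefficient picks up about ln(1 + t) × b, where b is the slope of semester on exposure.
- Ignoring within-person correlation: b = 0.486/0.2222 = 2.19.
- Using within-person contrasts only: a person's mean exposure is uniform on 0 to 1, with variance 1/12 = 0.0833, so within-person variance is 0.2222 - 0.0833 = 0.1389 and b = 0.486/0.1389 = 3.50.

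A compound-symmetry GEE lies between the two. For t = +5% the bracket is 1.05^2.19 = 1.11 to 1.05^3.50 = 1.19. For t = -5% it is 0.95^2.19 = 0.89 to 0.95^3.50 = 0.84.

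**Step 3: the planned model.** Solving the large-sample GEE equations over the three enrolment patterns and three working correlations gives:

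| Assumed trend per semester | Exposure only | Exposure + semester factor |
|---|---|---|
| -5% | 0.85 to 0.88 | 1.00 |
| -2% | 0.94 to 0.95 | 1.00 |
| 0% | 1.00 | 1.00 |
| +2% | 1.05 to 1.07 | 1.00 |
| +5% | 1.12 to 1.17 | 1.00 |

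A separate simulation gave 0.89 and 1.18 for -5% and +5% with exposure only. With semester added it gave 0.99 and 1.04, both within sampling error of 1. Taking the two together, the ranges at ±5% are 0.85-0.89 and 1.12-1.18.

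**Step 4: with a real effect.** In simulated data with a true rate ratio of 0.90 and uniform enrolment, the exposure-only model returned 1.02 under a +5% trend and 0.75 under a -5% trend. With semester added it returned 0.90 and 0.91.

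**Step 5: what semester does not remove.** These are again assumed scenarios with no true effect. Individual progression of 5% per semester, timed from a person's own enrolment, gives 1.21-1.22 without semester and still 1.10-1.13 with it. A doubling of the rate in the six months before enrolment still gives 0.66-0.71 with semester in the model.

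**The case against.** The strongest reply is that this is not where the SAP looks for its answer. Section 3.3.1 makes the matched comparison primary, and its controls are chosen within the same enrolment period, so calendar time is largely dealt with there. A reader might infer that the SAP's headline estimate is biased by trend; the document does not support that. This objection stands and lowers the severity.

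The SAP also does not ignore time. Section 3.2.1 plots rates with confidence intervals by six-month period, overall and by enrolment semester, and the sensitivity analysis includes semester. A strong trend would probably be seen. Seeing it, however, does not give a corrected estimate, and none is specified.

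The sizes depend on trends that the SAP does not give. A trend of ±5% per semester compounds over five steps to 1.05^5 = 1.28 or 0.95^5 = 0.77. At ±1% the false ratio, under uniform enrolment, is only about 0.97-0.98 or 1.02-1.03. This is fair: the mechanism is certain, the size is not.

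Three further inferences go too far:
- That the interaction model yields six semester-specific effects. This presumes factor coding, which the SAP does not state. With a linear term there would be an exposure term and a slope, though still no single time-adjusted effect.
- That seasonality is a large part of the problem. Six semesters are three whole years. A rate 10% higher in every second semester shifts the ratio by only 2-3%, and 20% higher by 4-5% (uniform enrolment).
- That exposure can never fall. The SAP states no exit but does not expressly exclude one.

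**Conclusion.** The point holds for the supporting time-dependent analysis. Its main model attributes any common calendar trend to the program, the adjusted version does not correct this, and the one analysis containing semester gives no single time-adjusted effect. A trend as small as 2% per semester produces a false rate ratio of about 0.94-0.95 or 1.05-1.07, and 5% about 0.85-0.89 or 1.12-1.18. The bias can create, hide or exaggerate an apparent benefit. If there is no trend, it is absent.

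These figures rest on a log-linear trend shared by all participants, on no exit from the program, and on assumed enrolment patterns, event rate and within-person correlation. A reader might also infer that adding semester would deal with disease progression; step 5 shows that it does so only in part. Severity is moderate, because the primary estimate of program effect comes from elsewhere.

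**What to change.** In section 3.2.3, make the main time-dependent model exposure proportion plus semester as a six-level factor, and carry the same terms into the adjusted version in section 3.2.4. Keep the exposure-by-semester interaction as the sensitivity analysis.

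Add a sentence saying what the change achieves: it removes trends common to all participants, removes only part of individual disease progression, and does not remove regression to the mean around enrolment.

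The cost is about two lines of text and no new data. Precision falls: the standard error of the log rate ratio is about 1.4 times larger. For example, in a simulated fit of 6,000 participants with back-loaded enrolment and a +5% trend, the 95% interval went from 1.110-1.209 to 0.969-1.095, and ln(1.095/0.969)/ln(1.209/1.110) = 0.122/0.085, or about 1.4.

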### 3.2.4 *Adjusted analyses*

Both the before-after and the time-dependent analyses will be performed without and with adjustment. Potential covariates will include LHD, age, gender, aboriginality, ARIA, SEIFA, target conditions, SF1 and previous patterns of service utilisation (number of hospitalisations in 2010, number of unplanned hospitalisations in 2010, number of avoidable hospitalisations in 2010 and number of ED admissions in 2010).

Each potential covariate will first be analysed using a univariate Poisson regression and only those with a univariate p-value smaller than 0.20 will be included in the final model. To avoid problems due to colinearity, in case of two covariates with a Pearson correlation coefficient greater than 0.8, only the one with the smallest univariate p-value will be kept in the final model. For covariates with more than 10% of data missing, we will create a separate category labeled “missing”.

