### 1.2 APDC

The APDC dataset will contain every public and private hospital admission which occurring between January 2007 and December 2013 in NSW. CDMP participants will be flagged.

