### 3 Evaluation of efficacy outcomes

#### 3.1 Efficacy outcomes

The primary efficacy outcome will be the rate of avoidable hospitalisations. Avoidable hospitalisations are defined as hospitalisations that fall under any of the following categories:

1. Vaccine-preventable:
  - "Influenza and pneumonia" (where any of the diagnosis fields have ICD-10-AM code as J10, J11, J13, J14, J15.3, J15.4, J15.7, J15.9, J16.8, J18.1, J18.8 excluding those where secondary diagnosis is D57)
  - "Other preventable vaccine" (where any of the diagnosis fields have ICD-10-AM code as A35, A36, A37, A80, B05, B06, B16.1, B16.9, B18.0, B18.1, B26, G00.0, M01.4)
2. Chronic:
  - "Diabetes complications" (where any of the diagnosis fields have ICD-10-AM code as E10.1-E10.8, E11.0-E11.8, E13.0-E13.8, E14.0-E14.8)
  - "Nutritional deficiencies" (where principal diagnosis has ICD-10-AM code as any of E40-E43, E55.0, E64.3)
  - "Iron deficiency anaemia" (where principal diagnosis has ICD-10-AM code as any of D50.1-D50.9)
  - "Hypertension" (where principal diagnosis has ICD-10-AM code as any of I10, I11.9)
  - "Congestive heart failure" (where principal diagnosis has ICD-10-AM code as any of I11.0, I50, J81)
  - "Angina" (where principal diagnosis has ICD-10-AM code as any of I20, I24.0, I24.8, I24.9)
  - "Chronic obstructive pulmonary disease" (where principal diagnosis has ICD-10-AM code as any of J41-J44, J47 or the principal diagnosis ICD-10-AM code is J20 with secondary diagnosis as J41, J42, J43, J44, J47)

- "Asthma" (where principal diagnosis has ICD-10-AM code as any of J45, J46)
3. Acute:
- "Dehydration and gastroenteritis" (where principal diagnosis has ICD-10-AM code as any of E86, K52.2, K52.8, K52.9)
  - "Convulsions and epilepsy" (where principal diagnosis has ICD-10-AM code as any of G40, G41, O15, R56)
  - "Ear, nose and throat infections" (where principal diagnosis has ICD-10-AM code as any of H66, H67, J02, J03, J06, J31.2)
  - "Dental conditions" (where principal diagnosis has ICD-10-AM code as any of A69.0, K02-K06, K08, K09.8, K09.9, K12, K13)
  - "Perforated/bleeding ulcer" (where principal diagnosis has ICD-10-AM code as any of K25.0-K25.2, K25.4-K25.6, K26.0-K26.2, K26.4-K26.6, K27.0-K27.2, K27.4-K27.6, K28.0-K28.2, K28.4-K28.6)
  - "Ruptured appendix" (where any of the diagnosis fields have ICD-10-AM code as K35.0)
  - "Pyelonephritis" (where principal diagnosis has ICD-10-AM code as any of N10, N11, N12, N13.6)

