## 3.3 *Analyses using a control group*

### 3.3.1 *Matched analyses*

The primary analysis for assessing the effect of the program will be performed using a propensity-matched cohort as the comparator.

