#### *Propensity scoring and matching*

Using baseline characteristics, we will calculate a propensity score defined as the probability of getting enrolled in the program. Matched controls will be selected from the APDC dataset using individuals who never got enrolled into the program. We will follow the following steps:

- Step 1:** Group program participants by period (e.g. month/quarter/semester) according to their enrolment date (the final “grouping period” will depend on the number of participants recruited).
- Step 2:** For each stratum/period, obtain details of the latest hospitalisation occurring in the 12 months preceding the period. Any program participant with no hospitalisation in the preceding 12 months will be excluded from propensity-based analyses.
- Step 3:** Within each stratum/period, calculate propensity score using a logistic regression modeling the probability of getting enrolled in the program. Covariates will include all variables considered for adjusted analyses.
- Step 4:** Within each stratum/period, starting with the earliest period, match 2 non-CDMP participants for each CDMP participant on the propensity score using optimal matching procedures. A control which has been used as a match in an earlier period is no longer available as match for a future period.
- Step 6:** Check the quality of the matching by plotting the propensity score distribution between the cases and controls overall and by period and by calculating the standardised difference for every covariate included in the propensity score calculation.

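### The propensity score for the primary matched analysis has no comorbidity measure built from the hospital diagnosis fields, and the planned balance check could not show any imbalance in disease burden left by this

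*SAP*

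**What the plan says.** SAP section 3.3.1 gives the matched comparison primary status: "The primary analysis for assessing the effect of the program will be performed using a propensity-matched cohort as the comparator". The comparators come from the hospital data: "Matched controls will be selected from the APDC dataset using individuals who never got enrolled into the program".

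Step 3 of the matching procedure has no covariate list of its own. It refers back: "Covariates will include all variables considered for adjusted analyses". The list meant is in section 3.2.4: "Potential covariates will include LHD, age, gender, aboriginality, ARIA, SEIFA, target conditions, SF1 and previous patterns of service utilisation". The utilisation items are then spelled out as "number of hospitalisations in 2010, number of unplanned hospitalisations in 2010, number of avoidable hospitalisations in 2010 and number of ED admissions in 2010".

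On the data held, section 1.2 states: "The APDC dataset will contain every public and private hospital admission which occurring between January 2007 and December 2013 in NSW", with program participants flagged. Section 3.1 builds the primary outcome from principal and secondary diagnosis codes. Several categories, including diabetes complications, apply "where any of the diagnosis fields have ICD-10-AM code as" one of the listed codes.

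Step 2 extracts details of each person's most recent admission in the year before the matching period, but Step 3 does not name those details as covariates. Step 6 plots the score and computes standardised differences for the variables in the score only.

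**The concern.** The list in section 3.2.4 was drawn up for the analyses of the participant cohort. In the before-after analysis each participant serves as their own comparator, so stable disease burden largely drops out. In the matched analysis different people are compared, and burden must be balanced by the score.

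If participants and their matched controls differ in comorbidity after matching, the rate ratio for avoidable hospitalisations mixes that difference with the program effect. Comorbidity can act in two ways. It can raise the number of admissions. It can also change which admissions count, because a diabetes-complication code in any diagnosis field makes an admission avoidable under section 3.1 even when the patient came in for something else.

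At stake is whether the primary estimate can be read as a program effect, and whether the SAP's own diagnostics would warn the analyst if it cannot.

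**Working it through.** The SAP gives no figure for this point, so there is none to reproduce. The check has two parts.

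**1. What the score contains on disease burden, and for whom**

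| Item in the score | Basis in the SAP | Limit |
|---|---|---|
| Target conditions | Listed in section 2.2 as a participant characteristic | No coding rule or source given for controls; covers the program's own conditions, not other disease |
| SF1 | Listed in section 2.2 as a participant characteristic; not defined | No source given for controls |
| Avoidable hospitalisations in 2010 | Defined from diagnosis codes in section 3.1; computable for both groups | Calendar 2010 only; counts qualifying admissions, not comorbid conditions |
| All and unplanned hospitalisations, ED admissions, in 2010 | Computable for both groups | Calendar 2010 only; indirect markers |
| Comorbidity index or diagnosis count | Not listed | – |
| Latest hospitalisation (Step 2) | Extracted | Not named as a covariate in Step 3 |

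Age of the counts: section 1.1 takes enrolments from January 2011 to December 2013. The count window closes on 31 December 2010. For a January 2011 enrolee it has just closed. For a December 2013 enrolee it closed nearly three years earlier, and disease that appeared in 2011 to 2013 is not in it.

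Feasibility: the earliest matching period starts in January 2011, so a 12-month look-back reaches January 2010 and a 2-year look-back reaches January 2009. Both lie inside the hospital data, which start in January 2007. Step 2 already excludes participants without an admission in the prior 12 months, so every matched participant has at least one coded admission in that window.

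**2. How much an omitted marker could matter (illustration only)**

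Take one binary marker of high comorbidity, with prevalence p1 in participants and p0 in controls after matching, and rate ratio RR for the outcome given the other covariates. With no program effect, the expected rate ratio is

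(1 + p1(RR − 1)) / (1 + p0(RR − 1)).

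All inputs below are assumptions; none comes from the SAP.

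- Equal prevalence: 1.00 for any RR.
- 50% versus 45%, RR 1.5: 1.25/1.225 = 1.02. RR 2: 1.50/1.45 = 1.03. RR 3: 2.00/1.90 = 1.05.
- 40% versus 30%, RR 1.5: 1.20/1.15 = 1.04. RR 2.5: 1.60/1.45 = 1.10.
- Reversed, 30% versus 40%, RR 1.5: 1.15/1.20 = 0.96. RR 2.5: 1.45/1.60 = 0.91.

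A ratio above 1 works against the program and could hide a benefit. A ratio below 1 could create an apparent benefit. The SAP gives nothing from which to choose among these rows.

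**The case against.** The score is not empty of disease information. Target conditions is a disease variable, and the 2010 count of avoidable hospitalisations is itself derived from diagnosis codes, is available for both groups, and is the primary outcome measured earlier. Matching on it, on three other utilisation counts and on demographics may remove much of the difference in burden. This stands. A reader might infer that the score has no comorbidity or severity content at all; the documents do not support that.

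A reader might also infer that participants are sicker than controls with the same utilisation, so that the primary comparison is certainly confounded against the program. No section says so. Section 2.2 lists program consent and reasons for non-enrolment, so selection could run either way. Only a risk can be shown, and any illustration must include the null and the reversed case.

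The argument about the borrowed list also has a limit. The time-dependent analysis in section 3.2.3 pools early and late enrolees with different exposure, so between-person differences enter there too. The within-person argument holds cleanly only for the before-after analysis.

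Finally, it can be said that one more covariate is a matter of preference, and that a source for SF1 and target conditions in controls may be set out elsewhere. The second part is possible. But the SAP does fix the covariates of its primary analysis, and as written the items certain to be available for controls on disease burden are the 2010 counts. The balance check cannot test whether those are enough. That part of the concern remains.

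**Conclusion.** The point holds as a gap in the specification of the primary analysis. The score has no dedicated comorbidity measure from diagnosis data already held for both groups. Its direct health items have no stated source for controls, and its utilisation counts age by up to about three years across the enrolment period. Residual confounding by disease burden may remain, of unknown size and direction, and Step 6 would not show it.

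Under the assumed inputs the effect on a null rate ratio runs from none (1.00) to 1.02–1.05 or 1.04–1.10, with bias below 1 if the imbalance is reversed (0.91–0.96 for the second pair of prevalences). These figures rest on imbalance remaining after matching on the listed covariates and on rate ratios conditional on them. They show that the issue could matter, not that it does. The change should be made because it is cheap and makes the question testable; the analysis is not shown to be invalid.

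**What to change.** In Step 3, add for participants and controls alike:

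- one comorbidity index named in advance (for example Charlson), computed from all APDC diagnosis fields in a fixed look-back that ends at the start of each matching period, for example the 12 months already used in Step 2;
- a broad principal-diagnosis group for the latest hospitalisation extracted in Step 2.

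Report both in the Step 6 standardised differences, overall and by period. State whether the look-back for the index changes when the sensitivity analyses vary the baseline period. In the same edit, say how target conditions and SF1 are obtained for controls, or refer to where this is set out.

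The cost is SAP wording and a standard coding algorithm; no new data are needed. The downside is a few more parameters in a logistic model fitted separately in each stratum. Step 1 leaves the strata open between month, quarter and semester, so the diagnosis groups should be broad and the strata not too small.

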## 1 Data sources

### 1.1 The Chronic Disease Management Program Minimum Data Set

The analysis will include every participant recorded in the program minimum dataset and enrolled between January 2011 and December 2013. The date of enrolment will be calculated using the following approach: If the Program consent date is available, it will be used as the enrolment date. If it is missing, and the Enrolment decision date is available, then this date will be used. If this is also not available, then the Registration date will be used as enrolment date instead.

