### 2.2 Description of CDMP participants

We will describe baseline characteristics of CDMP participants overall and broken down by year of enrolment (2011, 2012 and 2013). Baseline characteristics will include:

- Age
- Gender
- Aboriginality
- ARIA
- SEIFA

- Source of referral
- Target condition(s)
- Risk of hospitalisation
- Special population flag
- Initial SF1
- Initial intervention
- Reasons for non-enrolment
- Referral target
- Program consent
- Data use consent
- Number of hospitalisations in 2010, average length of hospital stay, total hospital bed days
- Number of unplanned hospitalisations in 2010, average length of unplanned hospital stay, total unplanned hospital bed days
- Number of avoidable hospitalisations in 2010, average length of avoidable hospital stay, total avoidable hospital bed days
- Number of ED admissions in 2010 overall and by triage categories 1-5

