### 3.2.2 *Before-after analyses*

Before-after analyses using will compare the rate of hospitalisations before enrolment into the program to the rate after enrolment into the program. For the before-after comparison, only patients enrolled between January 11 and June 13 will be included while only counting events occurring between 1 July 2010 (6 months before January 11) and 31 December 2013 (6 months after June 13).

For the purpose of this analysis every program participant will therefore contribute 2 data points; one before enrolment and one after enrolment. The analysis will be a Poisson regression with the period (before vs after) as a fixed effect. Generalized estimating equations with a compound symmetry structure will be used to model the correlations between multiple measurements from each patient.

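### The primary propensity score measures prior utilisation in calendar 2010 for every enrolment stratum up to December 2013, so from 2012 on it holds no count of recent admissions

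*SAP*

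**What the plan says.** Section 3.2.4 lists previous patterns of service use among the candidate covariates, as four counts: "number of hospitalisations in 2010, number of unplanned hospitalisations in 2010, number of avoidable hospitalisations in 2010 and number of ED admissions in 2010". The year is the same for everyone.

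Section 3.3.1 says: "The primary analysis for assessing the effect of the program will be performed using a propensity-matched cohort as the comparator". Step 3 of the matching procedure fits the score within each enrolment stratum and says: "Covariates will include all variables considered for adjusted analyses". The 2010 counts are therefore the utilisation covariates in every stratum. Section 1.1 takes participants "enrolled between January 2011 and December 2013".

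Recent history appears in Step 2. For each stratum the analyst is to "obtain details of the latest hospitalisation occurring in the 12 months preceding the period", and "Any program participant with no hospitalisation in the preceding 12 months will be excluded from propensity-based analyses".

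Step 6 limits the standardised differences to covariates that are in the score. The matched analysis compares event rates after the matching period only. The sensitivity analyses vary the baseline period (6 months or 2 years are the examples) without saying that the 2010 counts change.

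For the cohort, the before-after analysis (section 3.2.2) works by "only counting events occurring between 1 July 2010 (6 months before January 11) and 31 December 2013", and section 3.2.4 applies the same covariate list to its adjusted version.

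**The concern.** A propensity score for entry to a programme should describe people as they were just before entry. Here the utilisation part of the score is current for someone enrolled in January 2011 and two to three years old for someone enrolled in 2013.

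Take a participant enrolling in January 2013 who had six admissions in 2012, and a potential control who had one. If both had one admission in 2010 and agree on the other covariates, the score treats them as interchangeable. Step 2 does not separate them, because it looks for the latest admission and not the number.

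If recent admissions make enrolment more likely, participants will on average have heavier recent use than their matched controls, and so a higher expected rate afterwards whatever the programme does. The primary rate ratio would carry that difference. Step 6 would not show it, because recent counts are not in the score. The analysis model would not absorb it, because it contains no comparison of the periods before matching.

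**Working it through.** The SAP gives no figure of its own on this point, so there is none to reproduce. The check is calendar arithmetic on the SAP's dates, followed by illustrations on assumed inputs.

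**1. How old the 2010 counts are.** Gap = stratum start minus 1 January 2011. Coverage = share of the 12 months before the stratum start that lies in 2010.

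| Stratum start | Gap (months) | Coverage |
|---|---|---|
| January 2011 | 0 | 100% |
| April 2011 | 3 | 75% |
| July 2011 | 6 | 50% |
| October 2011 | 9 | 25% |
| January 2012 | 12 | 0% |
| January 2013 | 24 | 0% |
| December 2013 | 35 | 0% |

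The SAP leaves the grouping period open. The last stratum starts at 35 months if strata are months, 33 if quarters and 30 if semesters. Coverage is zero in 24 of 36, 8 of 12 or 4 of 6 strata, which is two-thirds in each case.

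**2. Weight of the affected strata.** Assume uniform enrolment over 36 months, follow-up to December 2013 and no deaths. A person enrolled at month g then contributes 36 − g months.

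- Share of follow-up from 2012-2013 enrolment: (24²/2)/(36²/2) = 576/1296 = 44%.
- Mean gap weighted by follow-up: (36³/6)/(36²/2) = 36/3 = 12 months, against 18 months unweighted.

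**3. Possible size of bias.** All runs assume no programme effect, so an unbiased rate ratio is 1.0.

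*Illustration A.* Log-rates follow an AR(1) process with annual correlation 0.6 and SD 1. The log-odds of enrolment rise by 0.25 to 0.5 per admission in the last year. Only people with at least one recent admission are kept. Balancing on 2010 counts gives 1.33-1.71 (gap 1 year), 1.45-1.83 (2 years) and 1.44-1.85 (3 years). Balancing on last-year counts gives 1.00-1.06. With the mean set at 0.4 admissions per year, the same design gives 1.14-1.35 (1 year) and 1.16-1.42 (2 years).

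*Illustration B.* Mean 0.4 admissions per year, year-to-year log-rate correlation 0.7 or 0.9, log-odds rising by 0.3 or 0.6 per recent admission, and the Step 2 requirement applied.

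| Gap (years) | 2010 count, log-odds 0.3 | 2010 count, log-odds 0.6 |
|---|---|---|
| 0 | 1.03-1.05 | 1.02-1.09 |
| 1 | 1.16-1.18 | 1.46-1.47 |
| 2 | 1.07-1.11 | 1.57-1.58 |
| 3 | 1.18-1.19 | 1.61-1.68 |

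Matching on the preceding-12-month count gives 0.92-1.04 over all settings, scattered around 1.0 with simulation noise.

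*Illustration C.* Enrolment depends on underlying risk instead of the observed recent count. 2010 counts give 1.21-1.53 and last-year counts 1.14-1.28.

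**4. Before-after overlap.** 1 July to 31 December 2010 is 184 days, or 184/365 = 50% of the covariate year. As a share of the window before enrolment:

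- enrolled 1 January 2011: 184/184 = 100%
- enrolled 1 January 2012: 184/549 = 34%
- enrolled 30 June 2013: 184/1095 = 17%
- pooled person-time under uniform enrolment: about 29%

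In a simulated Poisson GEE with a person-time offset and no effect, the period rate ratio was 0.99-1.00 unadjusted, with the overlapping covariate, and with a non-overlapping one. The covariate's own rate ratio was about 1.35 with overlap and 1.33 without.

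**The case against.** **Recent admissions are not ignored.** A reader might infer that the match takes no account of them. That goes too far: Step 2 requires one in the preceding 12 months and collects details of the latest. For the earliest 2011 strata, calendar 2010 is itself the recent history. This narrows the point to the number and type of recent admissions, mainly from 2012 on.

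**The wording may leave room.** Step 3 says what covariates will include, which need not be exhaustive, and the planned variation of baseline periods suggests that a rolling baseline was in mind. Neither moves the 2010 counts or names a recent count, so the defect remains in the text.

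**The mechanism is assumed.** A reader might infer that recent admissions are known to drive enrolment. The SAP does not say how patients are selected. Risk of hospitalisation and source of referral are only items in the descriptive list of section 2.2. They make the mechanism plausible but do not establish it. The direction and size of bias depend on it.

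**The size is uncertain.** The ratios vary widely with assumed inputs, and none of the simulations includes the other score covariates (such as age, LHD, target conditions and SF1), which may remove part of the imbalance. Late enrollees contribute little follow-up. Where enrolment depends on the recent count, adjusting for that count is bound to look close to perfect; Illustration C shows that some bias can remain. All of this stands and limits the claim about magnitude.

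**The overlap is minor.** A reader might infer that conditioning on part of the outcome biases the before-after estimate. The covariate takes the same value in both of a patient's rows, and the simulated period ratio hardly moved.

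**The section 2.2 table is not wrong.** It is descriptive and labels its year openly.

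**Conclusion.** The point holds for the propensity score of the primary analysis and should be corrected before the match is run. From the SAP's own dates, the utilisation covariates cover none of the preceding 12 months in two-thirds of the strata. Under uniform enrolment without deaths, those strata carry about 44% of follow-up. The number and type of recent admissions are neither balanced nor checked.

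Whether this biases the result depends on enrolment being related to recent use, which is an assumption. If it is, the matched rate ratio is probably biased against the programme: about 1.1 to 1.85 with no true effect, depending on inputs. Counts over the preceding 12 months bring this to about 1.0 when enrolment depends on those counts, and leave some residual bias when it depends on underlying risk. The documents do not support a single figure within that range.

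The before-after overlap is real, but its effect on the period rate ratio is expected to be negligible. The time-dependent analysis is not affected by overlap, because its outcomes start in January 2011.

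**What to change.** In Step 3, replace the four 2010 counts with counts of all, unplanned and avoidable hospitalisations and ED admissions in the 12 months before the start of each matching period. Use the same date for the controls of that stratum. For a stratum starting in January 2011 this is calendar 2010, so nothing changes there. Include the new counts in the Step 6 standardised differences, and state that the baseline-period sensitivity analyses vary this window too.

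As a minor correction, in the adjusted before-after model end the utilisation covariate window by 30 June 2010, or drop those covariates there. The earlier window is up to 36 months old for June 2013 enrollees. That matters little here, because the covariate does not differ between a patient's two rows. The time-dependent model can keep calendar 2010.

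The cost is SAP wording and programming. Sections 1.2 and 1.3 give hospital and ED data from January 2007, which covers a 12-month window for every stratum and the 2-year sensitivity window as well.
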